# Effect of dietary prebiotic supplementation on advanced glycation, insulin resistance and inflammatory biomarkers in adults with pre-diabetes: a study protocol for a double-blind placebo-controlled randomised crossover clinical trial

**DOI:** 10.1186/1472-6823-14-55

**Published:** 2014-07-10

**Keywords:** Advanced glycation end products, Maillard reaction, Prebiotics, Gut microbiota, Type 2 diabetes mellitus, Insulin resistance, Inflammation

## Abstract

**Background:**

Advanced glycation endproducts (AGEs) contribute to the development of vascular complications of diabetes and have been recently implicated in the pathogenesis of diabetes. Since AGEs are generated within foodstuffs upon food processing, it is increasingly recognised that the modern diet is replete with AGEs. AGEs are thought to stimulate chronic low-grade inflammation and promote oxidative stress and have been linked to the development of insulin resistance. Simple therapeutic strategies targeted at attenuating the progression of chronic low-grade inflammation and insulin resistance are urgently required to prevent or slow the development of type 2 diabetes in susceptible individuals. Dietary modulation of the human colonic microbiota has been shown to confer a number of health benefits to the host, but its effect on advanced glycation is unknown. The aim of this article is to describe the methodology of a double-blind placebo-controlled randomised crossover trial designed to determine the effect of 12 week consumption of a prebiotic dietary supplement on the advanced glycation pathway, insulin sensitivity and chronic low-grade inflammation in adults with pre-diabetes.

**Methods/Design:**

Thirty adults with pre-diabetes (Impaired Glucose Tolerance or Impaired Fasting Glucose) aged between 40–60 years will be randomly assigned to receive either 10 grams of prebiotic (inulin/oligofructose) daily or 10 grams placebo (maltodextrin) daily for 12 weeks. After a 2-week washout period, study subjects will crossover to receive the alternative dietary treatment for 12 weeks. The primary outcome is the difference in markers of the advanced glycation pathway carboxymethyllysine (CML) and methylglyoxal (MG) between experimental and control treatments. Secondary outcomes include HbA_1c_, insulin sensitivity, lipid levels, blood pressure, serum glutathione, adiponectin, IL-6, E-selectin, myeloperoxidase, C-reactive protein, Toll-like Receptor 4 (TLR4), soluble receptor for AGE (sRAGE), urinary 8-isoprostanes, faecal bacterial composition and short chain fatty acid profile. Anthropometric measures including BMI and waist circumference will be collected in addition to comprehensive dietary and lifestyle data.

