## Methods/Design

### Study design and setting

This is a 6.5-month randomised crossover controlled clinical trial (RCT) in which adults aged 40–60 years with diagnosed pre-diabetes will be enrolled. Potential study participants will be identified from General Practice (GP) clinics throughout South Gippsland, Victoria. The study design is presented in Figure 1.

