### Exclusion criteria

Individuals previously diagnosed with type 1, type 2 diabetes or impaired renal function (eGFR <90 mL/min/1.73 m^2^), individuals with known gastrointestinal pathology (coeliac disease, inflammatory bowel disease), pregnant women, smokers, individuals who have taken antibiotics, dietary prebiotic or probiotic nutritional supplements within the previous three months, individuals taking aspirin or Vitamin B, individuals who have made major dietary or lifestyle changes in the previous three months, individuals who are unwilling to provide blood, urine and stool samples or are unable to attend their local pathology collection centre.

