### Intervention

Participants will be randomly assigned to receive either 10 g of chicory-derived inulin/oligofructose powder (kindly provided by Beneo-Orafti Active Food Ingredients, Belgium) (intervention) or 10 g of maltodextrin powder (placebo) daily. Previous studies have demonstrated the bifidogenic effect of daily consumption of 5 g and 8 g dietary inulin supplements [43]. The inulin and maltodextrin powders to be consumed are both tasteless and can be mixed into hot or cold liquids or semi-solid foods. Participants will be instructed how to incorporate their supplement into their usual diet, and advised to gradually increase their dose over ten successive days until the target dose is reached. This stepped escalation in supplement dose aims to minimise gastrointestinal discomfort for participants, as a sudden increase in dietary prebiotic intake may result in increased stool frequency, abdominal bloating and flatulence until the bowel adapts to the increased fibre intake [44]. Written instructions will also be provided. Participants will be advised to consume each dietary supplement daily for 90 days, and otherwise maintain their usual dietary intake and level of physical activity. Gastrointestinal tolerance to the dietary supplements will be indicated by each study participant using a visual analogue scale as described below.

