### Follow up visits

Visits to the GP clinic will be scheduled for each participant at the conclusion of both Intervention 1 and Intervention 2 treatment periods, in order to provide follow-up data. Information collected will include anthropometric measurements, dietary intake assessment and physical activity assessment. Each participant will complete a self-administered questionnaire designed to assess gastrointestinal tolerance to the dietary supplement. Completed questionnaires will be placed into sealed opaque envelopes in order to maintain blinding of the researcher collecting data during the follow-up visits. Participants will also be instructed to attend the local pathology centre to provide urine and stool samples, and have blood taken for analysis.

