### Laboratory investigations

Biological samples will be collected at baseline and at completion of each three-month supplement intervention period and stored at −80°C immediately after collection. Twenty ml of fasting venous blood will be collected from each participant by phlebotomy into a sodium fluoride EDTA tube, a heparin-lined vacuum tube and a clean glass test tube. Twenty-four hour urine collections and morning stool samples will be collected in sterile containers.

Serum, urinary and faecal CML will be measured using a competitive ELISA (AGE-CML ELISA, Microcoat, Penzberg, Germany) [49]. This assay has been validated [50], is specific, and shows no cross-reactivity with other compounds [49]. The within assay and between-assay coefficient of variation are both less than 5%, respectively. Methylglyoxal will be measured by HPLC. Serum total cholesterol and triglyceride concentrations will be determined by enzymatic colorimetric assay (Technicon Instruments, Ltd., New York, N.Y., USA), while HDL cholesterol will be determined enzymatically in the supernatant after precipitation of other lipoproteins with dextran sulphate-magnesium. LDL-cholesterol will be calculated using the Friedewald formula. Plasma glucose levels will be determined by using an automated glucose oxidase method (Glucose analyser 2, Beckman Instruments, Fullerton, California). Insulin will be measured by enzymatic colorimetry (WAKO Pure-Chemical Industries, Osaka, Japan). Insulin Resistance (IR) will be estimated by the homeostasis model assessment (HOMA) index as [FI × (fasting glucose/22.5)], where FI is insulin in microunits per millilitre and fasting glucose is in millimoles per litre [51,52]. HbA1c will be measured by autoanalyser (Roche Diagnostics, Mannheim, Germany). Plasma IL-6, MCP-1, E-selectin, hsCRP, TLR4, glutathione (GSH), and myeloperoxidase will be measured by commercial ELISA kits (Biosource International, Camarillo, CA, USA). Urine 8-isoprostanes will be measured by ELISA (Oxford Biomedical Research, MI, USA).

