### Statistical analysis

Outcome analyses will be undertaken on an intention-to-treat basis. Data will be presented as means ± SD. The Kolmogorov-Smirnov goodness-of-fit test will be used to test for normal distribution, and data not normally distributed will be log-transformed. Correlation analyses will be performed using the Pearson correlation coefficient. Significance of changes during the study will be assessed by comparing change of means between placebo and prebiotic treatment periods by paired sample t-tests. Trial data will be analysed using a linear mixed model design based on repeated measures to account for fixed factors such as treatment sequence (inulin – placebo vs placebo - inulin) and treatment period (intervention 1 vs intervention 2) in addition to participants as a random factor. Significant differences will be defined as a value of P < 0.05 based on two-sided tests. Any differences in physical activity levels, anthropometry, energy or nutrient intake during the course of the trial will be identified using ANOVA. Gastrointestinal symptom data obtained by visual analogue scale will be analysed using the Wilcoxon signed rank test. Effect sizes including 95% confidence intervals will be calculated for all significant outcomes. Data analysis will be performed using SPSS 20.0 software (SPSS, Chicago, IL).

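### The planned comparison of within-period changes has no described starting value for period 2; end-of-period values should be the response, and the two-week washout needs a stated basis

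*Protocol article*

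**What the plan says.** All references are to the protocol article.

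- **Washout** (Abstract, Methods/Design): "After a 2-week washout period, study subjects will crossover to receive the alternative dietary treatment for 12 weeks".
- **Entry rule** (Exclusion criteria): the trial excludes "individuals who have taken antibiotics, dietary prebiotic or probiotic nutritional supplements within the previous three months".
- **Period length**: 12 weeks in the abstract. The Intervention section says "Participants will be advised to consume each dietary supplement daily for 90 days".
- **Sampling** (Laboratory investigations): "Biological samples will be collected at baseline and at completion of each three-month supplement intervention period". Under Follow up visits, clinic visits are scheduled "at the conclusion of both Intervention 1 and Intervention 2 treatment periods". Neither section lists a visit or sample between the washout and the second supplement.
- **Analysis** (Statistical analysis): "Significance of changes during the study will be assessed by comparing change of means between placebo and prebiotic treatment periods by paired sample t-tests". The same section then names a linear mixed model with sequence and period among the fixed factors and participant as random. It does not say whether the model's response is a change or an end-of-period value, and it does not define the baseline for a period-2 change.
- **Sample size** (Sample size calculation): difference 0.4 micromol/L in serum CML, SD 0.4, 5% significance, 80% power, giving 18 participants, plus 12 for withdrawals.

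**The concern.** A change over period 2 needs a value at the start of period 2. The text schedules none, so the stated test and the stated sampling do not fit together. Whoever runs the analysis must pick a baseline, and the candidates do not estimate the same quantity.

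The washout bears on this. Participants given prebiotic first begin placebo 14 days after their last dose, while the entry rule treats earlier prebiotic use as relevant for three months. If some effect remains at the start of placebo, a change score from that point records its fading as a rise on placebo, and this is credited to the prebiotic. The size of the primary result is at stake.

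**Working it through.** **Planned sample size.** Read SD 0.4 as the within-person SD. The paired difference of two end-of-period values then has variance 2 × 0.4² = 0.32 (SD 0.566). A two-sided 5% paired t-test for a difference of 0.4 needs n = 18, with power 0.807 (0.804 on n − 2 degrees of freedom). The plan's figure is reproduced, and it is reproduced for a contrast of end-of-period values.

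**Timing.** 90 + 14 + 90 = 194 days, about 6.4 months, which fits "This is a 6.5-month randomised crossover controlled clinical trial (RCT"; 84 + 14 + 84 = 182 days is 6.0 months. The washout is 14 of about 91 days, or 15% of the entry interval. In the prebiotic-first sequence, the end-of-period-2 sample falls 14 + 84 = 98 to 14 + 90 = 104 days after the last prebiotic dose, beyond three months.

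**What each contrast estimates.** Let the true reduction be τ = 0.4, with equal numbers per sequence and period effects set aside. Let r be the share of τ still present at the value used to start period 2, and c the share still present at the end of period 2. Neither is given in the protocol; both are assumptions.

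1. *Change from a post-washout value, c = 0.* Prebiotic-first: prebiotic change −τ, placebo change +rτ, difference −τ(1 + r). Placebo-first: −τ. Average size: τ(1 + r/2). For r = 0, 0.25, 0.5 and 1 this is 0.40, 0.45, 0.50 and 0.60.
2. *Change from the end-of-period-1 sample, the last one listed.* The full effect is present at that sample, so r = 1 by construction. Prebiotic-first gives 2τ, placebo-first gives τ, and the average is (0.8 + 0.4)/2 = 0.60, or 1.5 times the truth, whatever the washout.
3. *Both changes from the original baseline.* The baseline cancels and the contrast is the end-of-period difference.
4. *End-of-period values.* Prebiotic-first: τ(1 − c). Placebo-first: τ. Average: τ(1 − c/2).

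A simulation of 20,000 trials with 9 per sequence gave mean estimates of 0.40 for end values, 0.50 for post-washout change at r = 0.5, and 0.60 for change from the end of period 1. With no treatment effect, rejection stayed near 5% for all three.

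**Precision.** With independent errors and SD 0.4, a contrast of changes with separate period baselines has variance 4 × 0.4². For an unbiased effect of 0.4, power at n = 18 is then 0.52, and 34 participants would be needed for 80%.

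**The sequence term.** In a two-treatment, two-period design, sequence is aliased with carryover. It can hint at carryover but cannot correct the treatment estimate. For carryover of half the effect (0.2), its two-sided 5% power is about 7–11% with 9 per sequence and 8–16% with 15 per sequence (within-person SD 0.4; assumed correlation 0.5 to 0).

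**Residue at the end of period 2.** With end-of-period values and n = 18 (16 degrees of freedom), power is 0.80, 0.76, 0.69 and 0.56 for c = 0, 0.1, 0.25 and 0.5. With all 30 completing, it is 0.96 at c = 0 and 0.80 at c = 0.5.

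**First-period comparison.** Within-person SD 0.4 and baseline correlation 0.5 (both assumptions) imply a total SD of √(0.16/0.5) = 0.566. After baseline adjustment it is 0.566 × √(1 − 0.25) = 0.490. At 15 v 15 the power is about 58%.

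**The case against.** The strongest reply is that change may mean change from the original baseline. That baseline cancels, the contrast is the end-of-period difference, and the samples behind it fall 98 to 104 days after the last period-1 dose. On this reading the analysis is sound and meets the protocol's own three-month interval. This stands as a possible reading, but the text does not select it, and wording about changes in each treatment period invites the others.

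A reader might also infer more than the documents support:

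- *That the washout contradicts the entry rule.* It does not. One screens uncontrolled prior exposure, including antibiotics and probiotics; the other follows a known supplement. The gap is unexplained, no more.
- *That carryover in the planned change scores hides a real effect.* The direction is the reverse: residue in a period-2 starting value exaggerates the effect. Dilution arises only if residue lasts to the end of period 2, and it then affects the end-of-period contrast too.
- *That the analysis ignores carryover altogether.* The mixed model has sequence and period terms. They are a weak signal and no correction, but they are there.
- *That false positives are inflated.* The simulation shows about 5% when there is no effect.

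Finally, this is a condensed article and its two figures are not shown. A post-washout sample may appear there, so the statement is only that the text lists none. A washout rationale may likewise sit in the full protocol; its absence alone would be a minor matter.

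**Conclusion.** The point holds in a limited form. The article fixes a test on period changes and a sampling schedule that, as described, supplies no starting value for the second period. Depending on the baseline chosen, a true effect of 0.40 is estimated as 0.40 (original baseline), 0.40 to 0.60 (post-washout value, r from 0 to 1) or 0.60 (end of period 1). The last figure needs no assumption about washout, only that the effect is fully present at the end of period 1 and gone by the end of period 2. How much carryover exists is unknown, because the protocol gives no value for r or c. The mismatch between washout and entry interval is a secondary inconsistency, softened by the timing of the end-of-period-2 samples. The defect threatens the size of the estimate rather than the validity of the test when there is no effect, and wording alone can repair it.

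**What to change.** 1. In Statistical analysis, make the end-of-period value the response for CML and MG, in the mixed model with treatment, period and sequence as fixed effects and participant as random. Drop the paired t-test on changes, or define it as the end-of-period difference. This matches the sample size calculation. It does not remove dilution by (1 − c/2) if residue persists to the end of period 2.
2. Add a baseline-adjusted comparison of the randomised groups at the end of period 1 as a sensitivity analysis, reported whatever the main result and not used as a gate for choosing between analyses. Its downside is clearly lower precision than the crossover (about 58% power at 15 v 15 under the assumptions above), so it may differ from the main estimate by chance.
3. Reconcile the washout in the abstract with the interval in Exclusion criteria and state the basis for the washout. No washout length is proposed here.

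The cost is a few sentences and one extra analysis on samples already scheduled.

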**Discussion:**

Prebiotics which selectively stimulate the growth of beneficial bacteria in the human colon might offer protection against AGE-related pathology in people at risk of developing type 2 diabetes.

**Trial registration:**

Australia and New Zealand Clinical Trials Register (ANZCTR): ACTRN12613000130763.

## Background

Advanced Glycation Endproducts (AGEs) are formed via the Maillard reaction, which consists of a complex network of non-enzymatic reactions involving the carbonyl groups of reducing sugars which react with the amino groups of proteins [1]. AGEs are generated *in vivo* as a normal consequence of metabolism, but their formation is accelerated under conditions where blood glucose is chronically elevated such as poorly controlled diabetes [2]. AGE formation is also increased in the presence of oxidative stress, which is frequently observed in individuals with the metabolic syndrome [3,4]. Overproduction of reactive oxygen species (ROS) can result in maladaptive responses including interruption of cellular glycolysis, which can generate highly reactive dicarbonyl compounds capable of rapid AGE formation [5].

Excessive AGE accumulation can lead to several pathophysiological consequences. AGE-modification of proteins results in changes in structure and/or function. For example, the AGE-modification of extracellular collagen reduces its elasticity and solubility, and results in increased stiffness, disturbed cellular adhesion and reduced turnover contributing to basement membrane thickening [6]. Intracellularly, AGE-modification of mitochondrial proteins is associated with suppression in the activity of respiratory chain enzymes and overproduction of ROS [7,8]. Indeed, glycated proteins provide stable active sites for catalysing the formation of free radicals [9]. Finally, AGEs are able to bind and activate a range of receptors, which then trigger a downstream cascade of pathogenic mediators. Interaction of AGEs with the Receptor for AGEs (RAGE) promotes activation of the transcription factor nuclear factor kappa-B (NF-κB), with subsequent upregulation of chemokines, such as MCP-1 and profibrogenic mediators such as TGFβ in addition to pro-inflammatory cytokines which are known to be involved in thrombogenesis, vascular inflammation and pathological angiogenesis. These RAGE-mediated events contribute to many of the long-term complications of diabetes [10]. AGE/RAGE ligation also promotes overproduction of ROS which can then activate NF-κB [11], a key driver of inflammation.

More recently, AGEs have been implicated in the pathogenesis of both type 1 and type 2 diabetes. Several studies have shown that AGEs are associated with insulin resistance [12,13], and can induce low-grade inflammation [14] and pancreatic beta cell dysfunction [15,16].

In contrast to endogenous AGE formation, AGEs are also absorbed by the body from exogenous sources such as cigarette smoke and through consumption of processed foods [17]. Since AGEs are generated within foodstuffs upon heating and food processing, it is increasingly recognised that the modern diet is replete with AGEs [18]. AGE-restricted diets can arrest the development of type 2 diabetes in animal models [19]. A recent study found that excess consumption of AGE-precursors in mice over several generations led to the development of insulin resistance [20]. Human trials have found that dietary AGE restriction can improve insulin sensitivity [21,22] and decrease markers of oxidative stress [23] or inflammation [24]. Further studies are required to confirm the long-term benefits of dietary AGE-restriction in humans [25]. However, simple, safe and effective interventions which prevent or minimise excessive AGE accumulation and subsequent AGE-related pathology in people with diabetes and/or in those at risk of developing the condition are warranted.

Interventions which influence the human intestinal microbiota are worthy of further investigation given that specific micro-organisms have the ability to significantly affect host metabolism. Gut bacteria play an important role in the host immune system, modulation of inflammatory processes, extraction of energy from the host’s diet, fermentation of dietary fibres to produce short-chain fatty acids, alteration of human gene expression, regulation of intestinal permeability, production of some vitamins and promotion of mineral absorption by the host [26-31]. Furthermore, the total quantity and relative proportions of distinct bacterial species found in the colon differ between lean and obese individuals as well as between individuals with and without diabetes [32,33].

It is thought that certain dietary AGEs are largely undigested by human gut enzymes and eventually enter the colon, where they may act as a growth substrate for detrimental bacteria such as some Clostridium and Bacteroides species [34]. Therefore it is conceivable that individuals who consume highly processed diets (which contain large quantities of AGEs) may adversely alter their colonic microbial composition, potentially enhancing their risk for the development of metabolic diseases such as obesity and type 2 diabetes [35].

Therapeutic manipulation of the gut microbiota and restoration of normobiosis could potentially reduce circulating AGE levels and improve the metabolic health of individuals at risk for the development of type 2 diabetes. Regular consumption of prebiotics to promote the growth of beneficial gut bacterial flora is one such avenue currently under investigation. Prebiotics are non-digestable plant-derived carbohydrates which confer health benefits to the host by acting as a fermentation substrate in the colon, stimulating the preferential growth and activity of a limited number of beneficial microbial species [36]. Supplementation of the human diet with prebiotic fructans such as inulin or fructo-oligosaccharides alters the bacterial composition of the large intestine by favouring the selective proliferation of beneficial lactic acid-producing species such as bifidobacteria and lactobacilli. Prebiotic-stimulated increases in intestinal Bifidobacterium species have been shown to attenuate the production of ROS and markers of inflammation in individuals consuming high fat diets [37].

While the complex interactions between diet, intestinal microbiota and host metabolism are still being elucidated, no studies have investigated the effect of dietary prebiotics on circulating AGE concentrations. This trial was designed to investigate the effect of a prebiotic dietary supplement on AGE accumulation and explore changes to the growth and activity of specific gut microbiota in adults diagnosed with prediabetes.

